***If any of the responses fall into the shaded area, exclude the patient from the study***

**APPENDIX 9. UMSP ENROLLMENT FORM.**

| **enrollment form** | | |
| --- | --- | --- |
| **1. Study**  **Number:** | **2. Treatment**  **Number:** | **3. Start Date:**  ***(dd/mm/yy)*** |

| 4.Patients name: |
| --- |
| 5. Father’s name: |
| 6. Mother’s name: |
| 7. Primary caregiver / guardian’s name and relationship (N/A if mother or father): |
| 8. Sub county of residence. |
| 9. Home parish: |
| 10. LC1/village: |
| 11. Home address and localising features: |
| 12. a) Phone number: Yes ___No ___  If yes: b) Phone number (s) and the owner(s): |
| Patient Information |
| 13. Anti-folate use in the last 4 weeks? Yes ______ No________Unknown__________ |
| 14. Does the patient use malaria preventive measures: Yes ___No ___Unknown ____  If yes, which measures are used?    a) Spray: Yes ___No ___  b) Coils: Yes ___No ___  c) Chemoprophylaxis: Yes ___No ___  If yes, which drug? ___________________________________  e) Bed net: Yes ___No ____  If yes, is the net treated? Yes ___No ___   How often does the patient sleep under the net?  Always____ Often / Sometimes____  h) Other protective measures ______________________________________________________________ |

### APPENDIX 10. Adverse Event Reporting Guidelines

On Day 0 perform a careful history and physical exam and record your findings on the case record form (CRF), grading the patient reported symptoms and exam findings according to the guidelines presented in Appendices 3 and 4. Record the hemoglobin value and grade (Appendix 5) on the CRF as soon as they are available. All Day 0 values will serve as the patient’s baseline.

On all follow-up days, assess and grade the patient-reported symptoms and physical exam signs according to the guidelines in Appendices 3 and 4. Record the follow-up hemoglobin results obtained on Day 28 (and any extra day) and grade according to the guidelines in Appendix 5.

At each follow-up visit, evaluate the CFR for any reportable adverse events. Review for symptoms, physical exam signs, and hemoglobin results that are > grade 2 and are new or worsening by comparing the grade assigned on the follow-up day to the previous day’s record.

If a new or worsening symptom, sign, or laboratory value is present (increasing grade compared to the previous day’s value and > grade 2), answer “YES” in the appropriate column for reporting adverse events on the CRF (otherwise, answer “NO”).

An adverse event is defined as any “untoward” (unfavorable or undesirable) medical occurrence in a patient who has received a medication that may or may not be related to this treatment. Any event (patient-reported symptom, physical exam finding, or laboratory value) that occurs after treatment with a study medication that is new or worsening from Day 0 should be considered a possible adverse event, regardless of whether you think that the treatment caused the event.

The following scenarios are examples of adverse events (AEs):

|  | **Day 0** | **Day 1** | **Day 2** |
| --- | --- | --- | --- |
| Nausea | 0 | 0 | 2 |

AE = nausea on Day 2

|  | **Day 0** | **Day 1** | **Day 2** | **Day 3** |
| --- | --- | --- | --- | --- |
| Nausea | 2 | 1 | 0 | 2 |

AE = nausea on Day 3

For each new / worsening event of > grade 2, the following information will be collected on the Adverse Event Record Form:

1. Description of event
2. Date of event onset
3. Date event reported
4. Maximum severity of the event
5. Maximum suspected relationship of the event to study medication
6. Is the event serious?
7. Initials of the person reporting the event
8. Was the event episodic or intermittent in nature?
9. Outcome
10. Date event resolved

The following definitions / guidelines should be used to complete this form:

**Description of event** = symptom, sign, laboratory abnormality

**Date of event onset** = If event occurs on Days 1-3, date of event onset is the same as date event reported. If event occurs after Day 3, estimate the date of event onset from patient history and/or data available on CRF

**Date event reported** = Date the event is first recorded on the adverse event (AE) form

**Maximum severity** = Record the grade of the event (rank on scale of 2-4: moderate = 2, severe = 3, life-threatening = 4). This column should be updated if necessary during follow-up to capture the maximum severity of the event. Changes should be made by marking through the original number with a single line, recording the new value, and placing your initials and the date the change was made next to the new result.

**Maximum suspected relationship with study medications** =

| **Classification** | **Definition** |
| --- | --- |
| Definite | Clear-cut temporal association, with laboratory confirmation, if indicated |
| Probable | Clear-cut temporal association, with improvement upon study agent withdrawal, and not reasonably explained by the subject’s known clinical state |
| Possible | Less clear temporal association, other etiologies possible |
| Unlikely | Less clear temporal association; relationship to study agent in doubt |
| None | Clearly related to other etiologies such as motor vehicle accident |

The following criteria will be assessed in order to establish the suspected relationship of the event to the study medications:

1. Timing of the onset of the event
2. New event vs. worsening of a condition present at baseline
3. Overall medical condition of the patient, including status of malaria

**Serious events** = the term “serious” depends on the outcome and/or actions taken in response to the event and is not directly related to the “severity” or intensity of the event. A serious event is one that is:

- Fatal
- Life-threatening
- Results in or prolongs hospitalization
- Requires medical or surgical interventions to prevent a serious outcome
- Results in significant or persistent disability or capacity

Any death that occurs during the study should be considered a serious AE, regardless of whether an AE had previously been reported for the patient. All serious events should be reported to the Kampala core facility staff immediately. They will assist you with management of the patient (including arranging transport of the patient to Kampala, if necessary), will be responsible for completing the serious AE report form, and will report the event to the appropriate review committees.

**Episodic or intermittent event** = At the final visit, the CRF will be reviewed in order to determine if a reported AE was episodic or intermittent in nature.

**Outcome** = Complete this on Day 28 and rank on a scale of 1-5: resolved without sequelae = 1, resolved with sequelae = 2, AE still present at study end/discontinuation = 3, subject died = 4, outcome unknown = 5.

**Date event resolved** = You are asked to complete this on Day 28 in case an event fluctuates in intensity (severity) during the course of follow-up. At the final visit, review the data on the CRF with the patient to determine the date that the event resolved. If they cannot remember the exact date, choose the date that is halfway between the date the event was last recorded as abnormal and the date that the event was recorded as normal. If a patient is still experiencing an AE on Day 28, consider consulting the Kampala core facility staff to discuss the plan for further follow-up vs. discharge from the study. Patients who are still experiencing an AE on Day 28 will be managed according to the following guidelines: a) if the AE is improving and is < grade 1 (mild), the patient will be discharged from the study and the date of resolution for the AE will be recorded as Day 28; b) if the AE is stable or worsening, the patient will continued to be followed until the AE resolves or improves.

**Management of serious adverse events**: Study coordinators in Kampala will be notified within 24 hours of any serious adverse event. A serious adverse event is one that is:

- Fatal
- Life-threatening
- Results in or prolongs hospitalization
- Requires medical or surgical interventions to prevent a serious outcome
- Results in significant or persistent disability or capacity

Any death that occurs during the study will be considered a serious adverse event, regardless of whether an AE had previously been reported for the patient. If indicated, the study patient will be transferred to the nearest district hospital for appropriate care, including any necessary laboratory investigations.

**Length of follow-up for adverse events (See Appendix 14)**

1. **AEs presenting during the 28-day follow-up period** - If a patient with a previously reported AE is still experiencing the AE on Day 28, or if a patient presents with a new AE on Day 28, the Kampala core facility staff should be notified to discuss the plan for further follow-up vs. discharge from the study. Patients with ongoing AEs on Day 28 will be managed according to the following guidelines:
   1. If the AE is “old” (previously reported on Days 0-27) and is < grade 1 (mild), the patient will be managed according to good medical practice and will be discharged from the study. The date of resolution for the AE will be recorded as Day 28.
   2. If the AE is “old” (previously reported on Days 0-27) and is > grade 1, the patient will be followed until the AE resolves, improves, or stabilizes.
   3. If the AE is new, the AE will be reported and the patient will be followed until the AE resolves, improves, or stabilizes.
2. **AEs presenting after Day 28** – If a patient presents with a new AE during a follow-up visit after Day 28, the new AE will be managed according to the following guidelines:
   1. If the AE is serious, and the relationship of the event to study medications is “NONE” or “UNLIKELY”, the patient will be managed according to good medical practice, but the AE will not be reported or followed.
   2. If the AE is serious, and the relationship of the event to study medications is “POSSIBLY”, “PROBABLY” or “DEFINITELY”, the AE will be reported and the patient will be followed until the AE resolves, improves, or stabilizes.
   3. If the AE is not serious, the patient will be managed according to good medical practice, but the AE will not be reported or followed.
3. **Serious AEs** – Any patient who experiences a serious AE should be followed until the AE resolves or improves (< grade 1). Please note that if a patient develops evidence of severe malaria or danger signs, and requires treatment with parenteral quinine +/- hospitalization, the symptoms / signs / laboratory abnormalities leading to the diagnosis of severe malaria will be classified as serious AEs. Although formal study follow-up is typically terminated when a patient is classified as a treatment failure, any patient with severe malaria / danger signs should be followed up to ensure their serious AE has resolved / improved, and data should be recorded on the Serious Adverse Event – Follow-up Form.
4. **AEs in patients classified as treatment failures** – Formal study follow-up ends when a patient is classified as a treatment failure (ETF or LTF), and patients should be treated with quinine and managed according to good medical practice. Additional follow-up for AEs in patients classified as treatment failures, is not typically indicated, unless the AE is serious, or is felt to be probably or definitely related to the study medications. The Kampala core facility staff should be contacted with any questions about follow-up of AEs in patients with treatment failure.

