|  | **Grade 1**  **MILD** | **Grade 2**  **MODERATE** | **Grade 3**  **SEVERE** | **Grade 4**  **LIFE-THREATENING** |
| --- | --- | --- | --- | --- |
| **Hearing** | *< 4 years: N/A*  > 4 years: Decreased hearing in one ear | *< 4 years: N/A*  > 4 years: Decreased hearing in both ears or severe impairment in one ear | *< 4 years: Any evidence of hearing impairment*  > 4 years: Severe impairment in both ears | N/A |
| **Nystagmus** | 3 or fewer beats of lateral nystagmus | More than 3 beats of lateral nystagmus | Sustained lateral nystagmus, any vertical or rotary nystagmus | N/A |
| **Tablet test** | Difficulty grasping tablet but able to pick up | Unable to pick up tablet without dropping | Unable to grasp tablet | N/A |
| **Heel-toe** | 2-4 years: Able to take at least 5 steps  > 4 years: Able to take at least 5 tandem steps | 2-4 years: Unable to take 5 steps  > 4 years: Unable to take 5 tandem steps | *2-4 years: Unable to walk*  > 4 years: Unable to perform tandem walk | N/A |
| **Romberg** | > 4 years: Unable to stand for 30 seconds with eyes closed | > 4 years: Unable to stand for 15 seconds with eyes closed | > 4 years: Unable to stand with feet together with eyes open or closed | N/A |
| **Clinical symptoms / sign** *(not otherwise specified)* | No therapy; monitor condition | May require minimal intervention and monitoring | Requires medical care and possible hospitalization | Requires active medical intervention, hospitalization, or hospice care |

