Appendix 16. UMSP Adverse Event Record Form

| **adverse event record form** | | | |
| --- | --- | --- | --- |
| **Patient**  **Initials:** | **1. Study Number: U**|___|___|___||___||___| | **2. Day 0 Date:** |___|___|/|___|___|/|___|___|  ***day month year*** | **3. Treatment Number:** |___|___|___| |

|  | ***Complete on day first reported*** | | | ***Complete on day first reported and update as needed*** | | | ***Complete on final day*** | | |
| --- | --- | --- | --- | --- | --- | --- | --- | --- | --- |
| **Event description (a)** | **Date of event onset (b)** | **Date event reported**  **(c)** | **Initials of person reporting** | **Maximum severity* (d)** | **Maximum relationship† (e)** | **Serious? ‡ *(Y/N)***  **(f)** | **Episodic?**  ***(Y/N)***  **(g)** | **Outcome †† (h)** | **Date event resolved‡‡ (i)** |
| **80.** |  |  |  |  |  |  |  |  |  |
| **81.** |  |  |  |  |  |  |  |  |  |
| **82.** |  |  |  |  |  |  |  |  |  |
| **83.** |  |  |  |  |  |  |  |  |  |
| **84.** |  |  |  |  |  |  |  |  |  |
| **85.** |  |  |  |  |  |  |  |  |  |
| **86.** |  |  |  |  |  |  |  |  |  |
| **87.** |  |  |  |  |  |  |  |  |  |
| **88.** |  |  |  |  |  |  |  |  |  |
| **89.** |  |  |  |  |  |  |  |  |  |
| **90.** |  |  |  |  |  |  |  |  |  |
| **91.** |  |  |  |  |  |  |  |  |  |
| **92.** |  |  |  |  |  |  |  |  |  |
| **93.** |  |  |  |  |  |  |  |  |  |
| **94.** |  |  |  |  |  |  |  |  |  |

*** d) Severity:** *Rank on scale of 1-4: mild = 1; moderate = 2; severe = 3, life-threatening = 4*

**† e) Relationship:** *Rank on scale of 0-4: none = 0; unlikely = 1; possible = 2; probable = 3; definite = 4*

**‡ f) Serious:** Criteria for serious AE: fatal, life-threatening, results in or prolongs hospitalization, results in significant or persistent disability or capacity requires medical / surgical intervention to prevent serious outcome. **If serious, report to Kampala core facility staff immediately. They will assist with patient management, assist with completion of serious AE forms, and report the AE if necessary.**

**††h) Outcome:** *Rank on scale of 1-5: resolved without sequelae = 1; resolved with sequelae = 2; AE still present at study end/discontinuation, but improving = 3; subject died = 4; unknown = 5*

**‡‡ i) Date event resolved:** *Complete on Day 28 – If AE still ongoing at end of follow-up, indicate in question (h).*

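### Appendix 10 has two conflicting rules for a reported adverse event still present on Day 28, and both date a discharged, ongoing event as resolved that day

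*Protocol*

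**What the plan says.** Appendix 10 deals with an AE still present on Day 28 in two places.

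**Rule A**, in the paragraph on the date an event resolved, has two branches:
- (a) "if the AE is improving and is < grade 1 (mild), the patient will be discharged from the study", with Day 28 entered as the resolution date.
- (b) "if the AE is stable or worsening, the patient will continued to be followed until the AE resolves or improves".

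**Rule B**, in the section on length of follow-up, is introduced as covering AEs ongoing on Day 28:
- Item 1.1 covers an AE already reported before Day 28 "and is < grade 1 (mild), the patient will be managed according to good medical practice and will be discharged from the study". It continues: "The date of resolution for the AE will be recorded as Day 28".
- Item 1.2 covers an AE already reported before Day 28 "and is > grade 1, the patient will be followed until the AE resolves, improves, or stabilizes".

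Contact with the core facility on Day 28 is something to consider under Rule A and something that should happen under Rule B.

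The coding also differs. The Appendix 10 guideline defines outcome code 3 as an AE still present at the end, without further condition. The form in Appendix 16 has "AE still present at study end/discontinuation, but improving = 3". The form's note on the resolution date tells staff to show an ongoing AE in the outcome column, question (h).

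**The concern.** Both rules are instructions to site staff, and neither is said to take precedence. Staff at several sentinel sites could follow the protocol exactly and still treat like patients differently: one followed after Day 28, the other discharged.

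Both rules also give a resolution date to an event that they describe as present. One form could then hold a resolution date together with a code saying that the event continues. Any summary of AE duration or persistence would treat the date as real. Safety and tolerability are among the study aims in Section 3.0, so these records should be right.

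**Working it through.** There is no plan figure to reproduce, and no formula applies. The check applies both rules to every state of a previously reported, non-serious AE on Day 28.

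**Reading of the grade limits.** I take the discharge limit as grade 1 or below. Grade 0 means absent, so a strict less-than sign would cover no ongoing AE, and an AE at exactly grade 1 would fall under neither branch of Rule B.

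| State on Day 28 | Rule A | Rule B | Result |
|---|---|---|---|
| Grade 1, improving | Discharge, dated Day 28 | Discharge, dated Day 28 | Agree, but a present AE is dated as resolved |
| Grade 1, stable | Follow | Discharge, dated Day 28 | Conflict |
| Grade 1, worsening | Follow | Discharge, dated Day 28 | Conflict |
| Grade 2+, improving | No branch applies | Follow | Gap in Rule A |
| Grade 2+, stable | Follow until better or gone | May stop because stable | Conflict |
| Grade 2+, worsening | Follow until better or gone | Follow, but may stop once stable | Different end points |

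Three of six states conflict directly, one has different end points, one has no Rule A branch, and one agrees.

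**Which AEs reach these states.** Section 7.2.3 gives an AE report form only to events graded moderate or worse, and the Appendix 10 instructions rank reported severity from 2 to 4. (The printed form shows a 1 to 4 scale, but those two passages decide who gets a form.) The grade 1 rows therefore concern AEs reported at grade 2 or above that have since fallen to grade 1. The clearest conflict is the stable grade 2+ AE. The second is the AE that fell to grade 1 and then levelled off, or cleared and returned at grade 1.

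**An example.** In Appendix 6, Table B, "Decreased hearing in one ear" is grade 1 for patients over 4 years; decreased hearing in both ears, or severe impairment in one, is grade 2. Take a three-arm patient over 4 years with a reported grade 2 hearing loss that is down to a one-ear decrease on Day 21 and unchanged on Day 28. Judged against Day 21 it is stable: Rule A follows, while Rule B discharges and enters Day 28 as the resolution date. If a severe one-ear loss is stable instead, Rule A continues and Rule B may stop.

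**Outcome codes.** Under the guideline's code 3, an ongoing AE of any course can be coded. Under the form's wording, a stable or worsening AE fits none of the five codes except 5 (unknown).

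**The case against.** The strongest reply is that little of this reaches the results, and most of that reply stands.

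- A reader might infer that persistent toxicity is lost from the data. The document does not support that. The clinical record form has a Day 28 column of grades, the AE form keeps maximum severity and an outcome code, and Section 7.2.3 keeps mild AEs in the analysis. The safety outcomes in Section 4.2.2 are proportions with an event within 28 days, which a resolution date does not change.
- A reader might infer that every mild AE ongoing on Day 28 gets a false date. An AE never above mild has no report form, and so no date to falsify.
- An AE reported at grade 2+ and now at grade 1 has improved since it was reported, so Rule A(a) may be met and the rules coincide. This holds if improving is judged against the worst grade. It fails if it is judged against the last visit, and the protocol does not say which applies. The stable grade 2+ conflict does not depend on this.
- The hearing example is narrow. The neurologic examination is scheduled only in the three-arm study, and below 4 years any hearing impairment is grade 3. A sign that is new on Day 28 is followed under item 1.3, and significant or persistent disability makes an AE serious.
- A reader might also see a clash among the serious-AE rules, since item 2.2 allows stopping at stability and item 3 does not. Item 2.2 is confined to new AEs presenting after Day 28 and can be read as an exception, so I do not rely on it.
- Appendix 14, to which the length-of-follow-up section refers, may settle the follow-up rule. Its flowchart is not in the text available. The two passages in Appendix 10 would still disagree.

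**Conclusion.** The point holds as an internal inconsistency that should be corrected. Rules A and B give different instructions in three of six Day 28 states, most clearly for a stable AE of grade 2 or above. Both enter a resolution date for an AE that is present, against the protocol's own code 3 and the form's instruction, and code 3 is worded in two ways.

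The consequence is uneven safety follow-up after Day 28, and false resolution dates and durations for AEs reported at grade 2 or above. The 28-day incidence outcomes do not change. The document gives no rate of AEs persisting to Day 28, so the number of patients cannot be estimated.

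The conclusion rests on reading the discharge limit as grade 1 or below. For the grade 1 conflicts it also rests on judging course against the preceding visit. Confidence is limited by the unseen Appendix 14 flowchart.

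**What to change.** 1. Reconcile the paragraph on the date an event resolved with items 1.1 and 1.2 of the length-of-follow-up section, and check Appendix 14 against the result. One rule should say who is followed after Day 28, when follow-up ends, against which visit the course is judged, and whether the core facility must be contacted. Which rule applies is for the investigators to decide.
2. Delete, in both places, the instruction to enter Day 28 as the resolution date of an AE that is still present. Leave the date blank and code the AE as ongoing.
3. Give code 3 on the Appendix 16 form the unrestricted meaning that it has in Appendix 10. Recording improving versus stable or worsening as well is optional.

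The cost is negligible: text edits to Appendices 10 and 16, and to Appendix 14 if its flowchart differs. No additional examination is needed to correct the date and code.

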### 4.0 STUDY DESIGN

### 4.1 Overall Design

These studies shall be randomised, single-blinded trials designed according to World Health Organization (WHO) guidelines for assessment of therapeutic efficacy of antimalarial agents in areas of intense transmission3 with slight modifications. The target population is residents of the catchment areas of the sentinel health centres. The available population is residents aged 6 months and above who have symptoms suggestive of malaria and a positive screening thick blood smear and who are referred to the clinics for screening. Subjects who meet the inclusion criteria and are enrolled in the trial will be randomised to treatment with one of the combination regimens and will be followed for 28 days. Repeat evaluations will be performed on days 1, 2, 3, 7, 14, 21, and 28 and will include assessment for the occurrence of any possible adverse event. Treatment efficacy outcomes will be assessed using modifications of WHO clinical and parasitological classification criteria (Appendix 3).

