### 4.2.2 Secondary outcome

The efficacy of the combination regimens will also be assessed by comparing the treatment groups as follows:

1. Proportion of patients with clinical failure (ETF/LTF) at 14 days of follow-up (Appendix 3)
2. Proportion of patients with parasitological resistance (RI/RII/RIII) at 14 and 28 days of follow-up (Appendix 3) to supplement results of clinical outcome and to facilitate comparison with historical data.
3. Proportion of patients with treatment failure according to new WHO guidelines (ETF/LCF/LPF) at 14 and 28 days of follow-up (Appendix 3).
4. Rate of fever clearance: presence or absence of objective fever (axillary temperature > 37.5C) or patient report of fever on days 1, 2, 3
5. Rate of parasite clearance: proportion of positive vs. negative thick blood smears on day 2 and day 3
6. Change in mean haemoglobin from day 0 to 28
7. Proportion gametocytemic: presence vs. absence of gametocytes on any follow-up thick blood smear; proportion gametocytemic on days 2, 3, 7, 14, 21, and 28.

The safety and tolerability of the combination regimens will be further compared as follows:

1. Incidence of serious adverse events (AEs): proportion of patients experiencing any serious AE in each treatment group during the 28-day follow-up period.
2. Incidence of AEs: proportion of patients experiencing any mild/moderate/severe/life-threatening AEs during the 28-day follow-up period
3. Incidence of AEs by specific sign or symptom during the 28-day follow-up period

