### 8.0 STATISTICAL CONSIDERATIONS

### 8.1. Sample size calculations:

The sample size calculations will be made for each study based on the estimated efficacy of the combination regimens to be studied in the given region. For the purposes of sample size calculation, the risk of clinical failure at 28 days will be the main outcome. If the null hypothesis states that there is no difference in clinical outcome between the treatment groups, we plan to test the alternative hypothesis that treatment with an alternative combination regimen (AQ/SP or AS/AQ) will decrease the likelihood of clinical failure at 28 days of follow-up. Calculations will be made using an α = 0.05 and a statistical power of 80% based on a two-sided test. Allowance will be made for a possible 10% loss to follow-up to ensure that an adequate number of patients complete the study. Based on this, the sample size for the various drug combinations is summarized below:

Sample size for the different drug combinations

| **Presumed level of resistance.** | Resistance to CQ/SP | Resistance to AQ/SP or AS/AQ | Number per group | Number per group adjusted for loss to follow up. |
| --- | --- | --- | --- | --- |
| High resistance community (urban areas) | 15% | 5% | 160 | 180 |
| Low resistance community (rural areas) | 10% | 2% | 162 | 180 |

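### Follow-up stops at clinical failure, but adverse events and gametocytes are compared as crude 28-day proportions, so these comparisons are mixed with efficacy and biased in an uncertain direction

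*Protocol*

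**What the plan says.** Protocol section 4.1 says that enrolled patients "will be randomised to treatment with one of the combination regimens and will be followed for 28 days". Section 4.2.2 uses that window for safety. Serious AEs are the "proportion of patients experiencing any serious AE in each treatment group during the 28-day follow-up period", and any AE and AEs by sign or symptom have the same 28-day window. Gametocytaemia is defined as presence on any follow-up smear and, by day, as the "proportion gametocytemic on days 2, 3, 7, 14, 21, and 28".

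Section 8.2 compares all dichotomous variables by chi-square or Fisher tests and makes no allowance for time observed.

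The stopping rule is in Appendix 10, under length of follow-up for adverse events, item 4: "Formal study follow-up ends when a patient is classified as a treatment failure (ETF or LTF". Items 3 and 4 make exceptions for serious AEs and for AEs judged probably or definitely related. These extend follow-up of an event already recognised. They schedule no visit or smear at which a new one could be found.

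**The concern.** The length of observation depends on clinical failure, which is the primary outcome and is expected to differ between arms. A crude proportion over a nominal 28 days therefore compares groups watched for different lengths of time.

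The event that ends observation can also be an AE. The any-AE and serious-AE comparisons then carry part of the efficacy result, and a reader could not tell a tolerability difference from a difference in failure. Safety and tolerability are part of the stated aim (section 3.0).

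For gametocytes, patients who fail miss later smears, and the protocol gives no denominator for the day-specific proportions.

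**Working it through.** **The plan's own figures.** Section 8.1 uses α = 0.05 and "a statistical power of 80% based on a two-sided test". The table rows are:

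- "High resistance community (urban areas) | 15% | 5% | 160 | 180"
- "Low resistance community (rural areas) | 10% | 2% | 162 | 180"

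The two-proportion formula gives 141 and 138 per group without continuity correction, and 160 and 162 with it, so the table reproduces. The plan also says "Allowance will be made for a possible 10% loss to follow-up": 160/0.9 = 178 and 162/0.9 = 180, consistent with the stated 180. The sample size is not in dispute. It supplies the failure rates used below.

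**Patients whose follow-up is cut short.** With 180 per group, 0.15 × 180 = 27 v 0.05 × 180 = 9. At low-resistance sites, 0.10 × 180 = 18 v 0.02 × 180 = 3.6.

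**Observation lost.** With failure proportion p and mean failure day t, the share of planned person-days lost is p × (28 − t)/28. The protocol does not give t, so it is assumed.

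| Mean failure day | 15% v 5% | 10% v 2% |
|---|---|---|
| 3 | 13.4% v 4.5% | 8.9% v 1.8% |
| 7 | 11.3% v 3.8% | 7.5% v 1.5% |
| 14 | 7.5% v 2.5% | 5.0% v 1.0% |
| 21 | 3.8% v 1.3% | 2.5% v 0.5% |

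**Effect on the any-AE proportion.** Assume the same true 28-day AE risk R in both arms, a constant hazard, and all failures on day t. The risk up to failure is F = 1 − (1 − R)^(t/28). Let q be the share of failing patients, among those with no earlier AE, whose failure visit records a new AE. The spurious difference (failing arm minus comparator) is

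(p1 − p2) × [F + (1 − F)q − R].

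Worked case with R = 30% and t = 14: F = 1 − √0.7 = 0.163.

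- q = 0: 0.10 × (0.163 − 0.30) = −1.37 points.
- q = 1: 0.10 × (1 − 0.30) = +7.0 points.
- The sign changes at q = (R − F)/(1 − F) = 0.163.

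Results at t = 14, in percentage points:

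| R | q = 0: 15% v 5% | q = 0: 10% v 2% | q = 1: 15% v 5% | q = 1: 10% v 2% | Sign changes at q |
|---|---|---|---|---|---|
| 10% | −0.5 | −0.4 | +9.0 | +7.2 | 5% |
| 30% | −1.4 | −1.1 | +7.0 | +5.6 | 16% |
| 50% | −2.1 | −1.7 | +5.0 | +4.0 | 29% |

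For t from 3 to 21 and R from 10% to 50%, lost time alone (q = 0) gives −0.2 to −4.3 points at 15% v 5%, and −0.2 to −3.4 at 10% v 2%.

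**Is q small or large?** The protocol points towards large for late failures:

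- Appendix 3 defines late failure by danger signs or severe malaria, or by fever or recent fever, with parasitaemia.
- Section 7.2.2 counts any sign or symptom that is new or worse than the previous record. Appendix 10 does so whatever the cause, and its second nausea example counts a symptom that resolved and came back.
- Appendix 5 grades subjective fever as moderate whenever present.
- Appendix 10, item 3, classes the findings behind a severe-malaria diagnosis needing parenteral quinine as serious AEs.

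q need not reach 1. An early failure on parasite count alone may bring no new symptom.

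**Gametocytes.** Section 7.1 requires a smear on any extra day and reads every thick smear for gametocytes, so carriage at an unscheduled failure visit is captured. The scheduled follow-up smears are Days 2, 3, 7, 14, 21 and 28. A patient failing on, say, Day 17 contributes four of these six plus the failure smear, and misses Days 21 and 28.

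**The case against.** **The effect is small.** At n = 160 per arm the standard error of a difference is √(2R(1 − R)/160): 3.4 points at R = 10% and 5.6 at R = 50%. Lost time alone, at Day 14 and 15% v 5%, gives 0.5 to 2.1 points, under half of that. This stands for AEs unrelated to malaria. It stands less well for any AE: at R = 30% and q = 1 the 7.0 points exceed the standard error of √(2 × 0.3 × 0.7/160) = 5.1.

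**Stopping at rescue is defensible.** Patients who fail receive quinine (section 7.3), so later events would not reflect the study regimen alone. This stands, and it is why the remedy changes the outcome definition and not the follow-up.

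**Section 4.1 is only an overview, and details may sit in an analysis plan.** The protocol does describe other early exits (sections 5.2 and 7.3), and a separate plan is not shown. But the protocol itself fixes both the 28-day measure and the crude test. It already recognises the problem for haemoglobin, which section 7.1 measures on Day 28 or at clinical failure. AEs and gametocytes have no matching rule.

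**Stronger readings.** A reader might infer that the failing arm will look too safe. The AE definitions do not support this, because failure itself often adds an AE or a serious AE. A reader might also infer that a real gametocyte difference is hidden by a known amount. The protocol gives no carriage rates and no denominator, and the failure-visit smear offsets part of the loss.

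**Conclusion.** The mismatch is real: 28-day outcomes, crude tests, and observation that ends at the event on which the arms are expected to differ. At the design rates, with mean failure assumed on Day 14, 7.5% v 2.5% or 5.0% v 1.0% of planned person-days are lost.

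The direction is not determined. Lost time alone lowers the failing arm's AE proportion by at most 4.3 points over the ranges examined. If most failures record an AE, the any-AE comparison turns against that arm by several points. These sizes rest on assumed failure days and AE risks, a constant hazard and equal true risk in both arms.

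For gametocytes, the day-specific results cannot be interpreted until the denominator is stated. Only secondary outcomes are affected. Asymptomatic parasitaemia does not end follow-up, so the issue is confined to ETF and LTF.

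**What to change.** - In section 4.2.2, define AE outcomes from first dose to the earlier of clinical failure or Day 28. Compare them by time to first event or rate per person-day.
- Add a Day 0-7 AE comparison, where less follow-up is lost to failure.
- Report AEs with and without malaria signs and symptoms recorded on the day of failure, to separate tolerability from efficacy.
- For gametocytes, use smears up to and including the failure visit. State the denominator as patients still followed and smeared, and describe later-day prevalences as conditional on not having failed.
- Reconcile sections 4.1 and 4.2.2 with Appendix 10.

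No new data are needed: the clinical record form holds the study day of failure and symptoms by visit, and the AE form holds onset dates for moderate and worse events. The cost is slightly more analysis, and results limited to the period before rescue treatment. The change does not make stopping at failure uninformative. It makes the comparison match what is observed.
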